### Data management and monitoring

The data were collected by the researchers of this study through the electronic medical record (EMR) system for participants' basic information and related laboratory tests. Participants will be assigned a uniform number to protect privacy. The data will be manually input by the researchers into the research database through EMR system, [name] and [name] have the permission to input, read and modify them and have the authority to conduct interim review and stop the experiment. All information related to the study will be securely stored at the study site. If necessary, members of sponsor units or government administrative departments can access the data according to their respective authority. The results will be published as statistical analysis data and will not contain any identifiable participants’ information. The conduct of the trial will be audited every 3 months by persons independent of the researchers, with no competing interests.

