### Primary outcomes

Primary outcomes of this cohort are major adverse cardiovascular events within 1 year, including in-stent restenosis, severe ventricular arrhythmia, heart failure, recurrent angina pectoris, and sudden cardiac death.

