#### Blood sample and data collection

Peripheral blood samples of these patients were obtained within 24 h of admission and collected in heparin anticoagulant tube (2–4 mL). Samples were placed at room temperature for testing within 24 h. Clinical data of patients such as age, gender, history of hypertension, coronary heart disease and diabetes mellitus, body mass index (BMI), white blood cell count, level of hemoglobin, platelet, creatinine, aspartate aminotransferase (AST), alanine aminotransferase (ALT), lipid profile, left ventricular ejection fraction, left ventricular end-diastolic volume etc. were collected. The results of coronary angiography were recorded as well.

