#### Follow-up

Patients will be followed up during hospitalization(t0), 3 months(t1), 6 months(t2) and 12 months(t3) after discharge through outpatient-clinic, hospitalization, telephone and other communication way. Content of follow-up is presented in Table 1.

**Table 1 Tab1:** Content of follow-up at different time points post-PCI

Assessments	t0	t1	t2	t3

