** LDL-C(≤ 1.4 mmol/L)**				
**Outcomes**				
In-stent restenosis				
Severe ventricular arrhythmia				
Heart failure				
Recurrent angina pectoris				
Sudden cardiac death				
No reflow				
Atrial fibrillation				
Death from other causes other than cardiac death				
Stroke/cerebrovascular accident				

Including daily living conditions (whether to follow a low-salt and low-fat diet, whether there is proper exercise, whether to quit smoking, drinking, etc.), and whether to use medications for secondary prevention for CHD, including antiplatelet agents, statins, angiotensin-converting enzyme inhibitor(ACEI)/angiotensin II receptor(ARB), β blocker, and whether the dose of ACEI/ARB and β blocker meets the recommended dose, blood pressure control(≤ 130/80 mmHg), blood glucose control(fasting blood glucose ≤ 6.0 mmol/L, 2 h postprandial blood glucose ≤ 11.0 mmol/L, or glycosylated hemoglobin ≤ 6.5%), control of low-density lipoprotein cholesterol(LDL-C) (≤ 1.4 mmol/L) and occurrence of MACE which including in-stent restenosis, severe ventricular arrhythmia, heart failure, recurrent angina pectoris, and sudden cardiac death. The content of follow-up also includes no reflow, atrial fibrillation, occurrence of death from other causes other than cardiac death, and stroke/cerebrovascular accident. The definition of all outcomes is presented in Table 2.

**Table 2 Tab2:** Definition of the outcomes

Events (during hospitalization or follow-up)	Definition
In-stent restenosis	In-stent restenosis is defined if it is observed during coronary angiography reexamination
Severe ventricular arrhythmia	Including ventricular tachycardia, ventricular fibrillation captured by ECG or ECG monitoring
Heart failure	The patients had typical symptoms of heart failure (such as chest tightness, dyspnea, etc.) combined with cardiac ultrasound suggesting decreased cardiac systolic or diastolic function or accompanied by elevated NT-proBNP
Recurrent angina pectoris	If symptoms that are similar or even aggravated to previous angina symptoms like location, time, and degree of pain still occur after PCI
Sudden cardiac death	Sudden cardiac death due to coronary heart disease
No reflow	No coronary reflow or slow flow is observed during PCI or coronary angiography reexamination
Atrial fibrillation	Paroxysmal or persistent atrial fibrillation captured by ECG or ECG monitoring

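### Two researchers hold read, edit, interim-review and stopping rights over the research database, with no stated separation of marker results from a partly judgement-based MACE

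*Protocol article*

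**What the plan says.** All references are to the protocol article.

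- **Access and authority** (Data management and monitoring). Two named researchers "have the permission to input, read and modify them and have the authority to conduct interim review and stop the experiment". The source is the electronic medical record, used for participants' "basic information and related laboratory tests". On the route into the database: "The data will be manually input by the researchers into the research database through EMR system". Only one database is described.
- **Oversight** (same section). "The conduct of the trial will be audited every 3 months by persons independent of the researchers, with no competing interests".
- **Exposure** (Blood sample and data collection). "Peripheral blood samples of these patients were obtained within 24 h of admission", with testing within a further 24 h.
- **Who collects outcomes, and how** (Abstract, Methods; Follow-up; Consent). The Abstract assigns outcome collection to local investigators. Follow-up takes place in hospital and at 3, 6 and 12 months after discharge, "through outpatient-clinic, hospitalization, telephone and other communication way". The Consent section also lists inpatient and outpatient records as a source.
- **Outcome** (Primary outcomes). MACE within one year, "including in-stent restenosis, severe ventricular arrhythmia, heart failure, recurrent angina pectoris, and sudden cardiac death". In Table 2, recurrent angina means "symptoms that are similar or even aggravated to previous angina symptoms" after PCI, with no objective criterion.

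**The concern.** The study asks whether immune markers measured at admission predict MACE. That needs outcomes to be recorded in the same way whatever the marker value. As the article describes it, marker values can be available before every post-discharge assessment, and the people with editing rights over the research database also have an interim review of unrestricted content and the power to stop. Nothing stated keeps marker values away from those who collect, code or edit outcomes.

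If a borderline symptom report is more readily counted, or an entry more readily changed, when the marker is known to be high, an association appears that is not biological. The Discussion says the authors expect these cell features to affect prognosis, so the expectation exists. An interim look at markers against outcomes, by people who can also stop the study, would add a data-driven decision to the same risk.

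**Working it through.** **1. Timing.** Sampling is within 24 h of admission and testing within a further 24 h, so marker results can exist by about 48 h. The assessments at 3, 6 and 12 months all come later.

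**2. How far each MACE component depends on judgement (Table 2).**

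| Component | Evidence required | Room for judgement |
|---|---|---|
| Recurrent angina | Symptoms only | Large |
| Heart failure | Symptoms plus ultrasound or NT-proBNP, no numeric threshold | Moderate |
| In-stent restenosis | Seen at repeat angiography, no stenosis threshold | Some |
| Severe ventricular arrhythmia | Captured on ECG or monitoring | Little |
| Sudden cardiac death | Attributed to coronary disease | Some, on cause |

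MACE is therefore partly, not mainly, judgement-based.

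**3. Expected events (Sample size section).** The cited rate is 151/1864 = 0.0810. With 150 enrolled: 150 × 0.081 = 12.2 events. After the planned 10% loss, 150 × 0.90 = 135 are followed: 135 × 0.081 = 10.9 events. The rate is borrowed from another cohort, and the article does not say that its MACE had the same components.

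**4. Illustration A: over-calling in the marker-high half only.** Assumptions: a median split, no true association, a true risk of 8.1% in both halves, and a fraction e of event-free marker-high patients recorded as MACE.

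Recorded risk, high half: pH = 0.081 + 0.919 × e. Low half: pL = 0.081. False events = (N/2) × 0.919 × e.

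With h = N/2, d = pH − pL and p̄ = (pH + pL)/2, let SE0 = √[2p̄(1 − p̄)/h] and SE1 = √[pH(1 − pH)/h + pL(1 − pL)/h]. The chance of two-sided P < 0.05 is Φ[(d − 1.96·SE0)/SE1] + Φ[(−d − 1.96·SE0)/SE1].

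| e (assumed) | pH | RR = pH/0.081 | False events, N = 135 / 150 | Chance of P < 0.05, N = 135 / 150 |
|---|---|---|---|---|
| 0 | 0.081 | 1.00 | 0 / 0 | 5% / 5% |
| 2% | 0.099 | 1.23 | 1.2 / 1.4 | 6.6% / 6.8% |
| 5% | 0.127 | 1.57 | 3.1 / 3.4 | 14.0% / 15.1% |
| 10% | 0.173 | 2.13 | 6.2 / 6.9 | 36.0% / 39.3% |

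For e = 5% and N = 150: d = 0.0460, SE0 = 0.0498, SE1 = 0.0497. The first term is Φ(−1.04) = 0.149 and the second is 0.002, which sum to 0.151.

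**5. Illustration B: over-calling in both halves, at unequal rates.** N = 135, so 67.5 per half; Wald test of the log odds ratio.

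- 5% low, 10% high: risks 0.127 and 0.173. OR = (0.1729/0.8271)/(0.1270/0.8730) = 1.44; chance of P < 0.05 is 11.6%.
- 5% low, 15% high: risks 0.127 and 0.219. OR = 1.93; chance 28.7%. This case is extreme: it implies 67.5 × 0.919 × 0.15 = 9.3 false events in the high half against 67.5 × 0.081 = 5.5 true ones.

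Both illustrations use normal approximations with few events and describe scale only. The documents give no recording-error rates.

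**The case against.** Several stronger readings are tempting, and the text does not support them.

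- *The same two people control marker results and outcomes alike.* The data management section names only basic information and laboratory tests. That flow-cytometry results and outcomes sit in the same database is plausible, because no other is described, but it is an inference.
- *Outcome callers know the marker values.* The Abstract gives outcome collection to local investigators at three centres, and nothing identifies them with the two database holders. Naming two people may even be meant to restrict access. The article says neither that assessors are masked nor that they are unmasked, and silence in a condensed article is not itself a fault.
- *An interim marker-by-MACE test is planned.* No such test and no results-based stopping rule is described. The study is non-interventional, with a planned enrolment of 150.
- *MACE is mostly subjective.* Only angina is defined by symptoms alone. The heart failure, restenosis and arrhythmia definitions call for imaging, a biomarker or an ECG.
- *The harm could never be undone.* ECGs, angiograms, scans and records could be re-read masked later. Angina reported by telephone could not.

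The illustrations can also be challenged. The rates are assumed, cut-offs are to be derived afterwards by ROC analysis, and with eight cell subsets and four markers, consistent bias along any one marker is hard to presume. That stands as a limit on the size, although a caller needs no formal cut-off to regard a value as high.

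What remains is a stated arrangement: editing rights, interim review of unspecified content and stopping authority in the same hands. Editing rights matter even if someone else makes the call. The audit covers conduct and was omitted from none of this reasoning; it neither hides marker values nor limits interim comparisons.

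**Conclusion.** The point holds in a limited form. The plan as written leaves a route by which knowledge of marker values could influence how outcomes are recorded or edited, and it puts no boundary on interim review. It does not show that this will happen.

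The route matters because the event count is small: about 11 to 12, if the borrowed 8.1% applies. Under no true effect, about three false events confined to the marker-high half would raise the chance of a nominally significant result from 5% to 14 to 15%, and one or two would raise it only to about 7%. These figures rest on assumed over-calling rates, a median split and a single marker. The true size of any bias is unknown and could be nil. This is a cheap improvement to the stated arrangement, not a demonstrated flaw in the results.

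**What to change.** 1. Hold flow-cytometry results in a separate file under the study number, closed to anyone who collects, codes or edits follow-up outcomes. Link it to the outcome data only after the 12-month outcomes are locked.
2. State that interim review covers recruitment, data quality and safety only, with no comparison of markers against outcomes.

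**Cost.** A change to database permissions and two sentences of text. No extra assessor, visit or patient is needed. The one drawback is that the marker-outcome analysis must wait until the outcomes are locked.

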### Modification of the protocol

Any modifications which may affect the conduction of this trial, including inclusion or exclusion criteria and outcome indicators will require a formal modification of the protocol. Modification will be agreed by the research group, approved by local Ethics Committee, and reported to participants, trial registrars, journals, and regulators.

### Additional supplementary instructions

This study is a non-interventional study, it will not involve vulnerable groups or interfere with routine diagnosis and treatment of participants, it will not affect any medical rights or increase the risk of participants either.

### Dissemination

This study has been registered in Chinese Clinical Trial Registry Center: ChiCTR2200066382. The dissemination will occur through the publication of articles in international peer-reviewed journals.

## Discussion

The purpose of this study is to investigate the characteristics of various subtypes of monocytes, macrophages, T cells and the expression of CD47, sirpα and S100A4 on these cells in peripheral blood of ACS patients and explore the relationship between these indexes and the occurrence of MACE 1 year later. ACS is the most dangerous type of CHD. The pathogenesis of ACS is long-term ischemia caused by coronary stenosis, obstruction or acute thrombosis, which eventually led to myocardial cell death [17]. Evidences indicated that the prognosis or MACE after ACS is related to inflammation process, in which innate immune system and acquired immune system are involved.

In inflammatory process, innate immune response is an important regulator, including three different stages in which the inflammatory stage is involved. The process of the response can release a variety of cytokines and call immune cells to the areas of inflammation. Cell necrosis causes sterile inflammation and triggers a cascade of intracellular biochemical signaling process in which MPS is involved [18]. So, after ACS, myocardial necrosis is implicated in innate immune response. The degree and duration of inflammation influence the development of post-ACS remodeling and heart failure. Lee et al. [19] constructed a mouse myocardial infarction model and discovered that the number of monocytes and macrophages increased through PET/MRI, flow cytometry and PCR.

Many researches focus on the potential therapeutic targets of the MPS after ACS. MPS consists of monocytes, macrophages and dendritic cells. Monocytes make up 10% of white blood cells which can recognize and engulf pathogens, infected cells, lipids, and cell debris. They also promote immune system responses by acquiring and presenting antigens, migrating to inflammatory sites and producing cytokines [20]. Classical monocytes in human, based on high expression of CD14 but absence of CD16, were described as CD14^++^CD16^−^. These monocytes may migrate to the site of damage and inflammation area and differentiate into dendritic cells and macrophages with higher phagocytosis and antibacterial ability, and presents antigens to T cells [21]. Compared with classical monocytes, the phagocytosis of non-classical mononuclear cells reduced. Non-classical monocytes do not perform the functions of classic monocytes, but patrolling blood vessel walls, promoting wound healing and responding to viral infections instead. Due to high expression of CD14 and low expression of CD16 in human, non-classical monocytes were also known as CD14^++^CD16^+^ [11]. Subsequently, a third subgroup of monocytes had been identified and known as intermediate monocytes, expressing both CD14 and CD16, were described as CD14^+^CD16^+^. This subgroup showed inflammatory properties likewise and may play a significant role in antigen presentation and rapid pathogen defense [22].

Macrophages are derived from monocytes in the peripheral blood. They could be differentiated into classical activated M1 type and selective activation M2 type macrophages according to different activation states and functions [23]. In the process of tissue inflammation, M1 appears in the early stage and will recruit many inflammatory cells to fight against pathogens, which is a pro-inflammatory effect. After the elimination of pathogens, M2 was used to inhibit the recruitment of inflammatory cells, which was an anti-inflammatory effect. M2 promotes both angiogenesis and tissue repair, allowing the tissue to return to its original state. Continuous M1-type activation causes tissue damage, leading to inflammatory disease. M2 type hyperactivation may lead to fibrosis due to tissue overrepair or even promote tumor growth through immunosuppression [24]. The surface markers of M1 and M2 cells are different. Several studies set a protocol to distinguished M1 and M2 based on the increasing expression of CD86 in both cell while expression of CD163 elevated solely in M2 cells [25, 26].

Inefficient clearance of necrotic cardiomyocytes may result in loss of collateral cardiomyocytes and expansion of infarction [27]. CD47 has been described as a “don’t eat me” molecule which prevents normal cells from macrophages phagocytosis [28]. Signal regulatory protein α(Sirpα), named as CD172a as well, is mainly existed on the surface of macrophages. After binding with “don’t eat me” molecule of other cells, sirpα, the ligand of CD47, can transmit inhibitory signals to macrophages and inhibit the phagocytosis of macrophages to target cells. Thus, this pathway can be used to distinguish self cells from non-self cells [29]. Zhang et al. [30] also found that high expression of CD47 during ACS impairs phagocytosis of macrophages which was consistent with the above theory, and suggested CD47 might be a potential target to promote the repair of the wound in ischemia heart.

The relationship between innate immune response and myocardial remodeling and ischemia–reperfusion injury after myocardial infarction has been studied in the past decades. But in the past few years, some studies have suggested that acquired immune response is also involved in these processes which brings us to T cells. T cells derives from bone marrow, they plays immune function by distributing to immune organs and tissues through lymph and blood circulation [31]. The subset of T cells are based on different surface marker. CD3^+^ represents for the sum of T cells, indicating the state of human immune function. The T-helper cells (Th cells) are CD4^+^ cells, meanwhile, the key to regulating the immune response. When ACS occurred, the account of CD4^+^ T cells might reduce due to cardiomyocytes necrosis, fibrosis, and systolic dysfunction and lead to heart failure [32]. CD8^+^ identifies cytotoxic T cells. CD8^+^ T cells from ACS patients suggest the increasing of cytotoxicity. With more quantity of CD8^+^ T cells, the larger of infarction area in ACS patients, which can also lead to insufficiency of ventricular function [33, 34]. The ratio of CD4 to CD8 can be used to judge the immune dysfunction. In addition, NKT cells are a type of lymphocyte, also known as natural killer cells, with NK cell receptors and T cell receptors on the cell surface. Research found that the account of NKT cells decreased in ACS patients and might be a useful predictor of prognosis after coronary stent implantation [35]. Tim-3 is a sign of T cell exhaustion. Several studies have found a link between tim-3 and heart disease. Zhang et al. [36] found that the elevation of tim-3 was associated with the aggravation of CHD. Another study also indicated that increasing expression of tim-3 might participate in the dysfunction of T cell during chronic heart failure [37].

Our previous study found that expression of S100A4 elevated in peripheral leukocyte of ACS patients. S100A4 is a polypeptide protein, mainly composed of 101 amino acids, belonging to the S100 protein family, in which there are a total of 21 identified members, and it is also one of the largest subfamilies of calcium ion binding protein family [12]. Studies have shown that S100A4 protein can promote tumor invasion and metastasis, regulating a variety of cell functions. When combined with calcium ion, S100A4 protein is a crucial key to differentiation, proliferation of cells, muscle contraction, inflammatory and apoptosis through the pathway of calcium ion signal transduction [38–40]. A study has shown that the level of S100A4 will increase in ACS patients, which may become a new biomarker to predict ACS [41]. S100A4 knockout can aggravate ventricular remodeling, myocardial fibrosis, and distal myocardial capillary density reduction in mice [42]. Whether elevation of S100A4 affects the prognosis of ACS patients is unknown yet.

In this study, we assume that the characteristics of various subtypes of monocytes, macrophages, T cells and the expression of CD47, sirpα and S100A4 on these cells in peripheral blood differs in ACS patients and will affect the prognosis of these patients, so this protocol were set to detect the account and distribution of classical monocytes, non-classical monocytes, intermediate monocytes, M1 type macrophages, M2 type macrophages, CD4 positive T cells, CD8 positive cells and NKT cells and the level of CD47, sirpα, tim-3 and S100A4 by detecting different surface markers through flow cytometry. Then primary outcomes are observed during hospitalization and 3,6 and 12 months after discharge of participants. It is expected that this study will reveal the possible targets to improve the prognosis or prevent from occurrence of MACE. Since it’s a multicenter study, the enrollment rate of participants will be accelerated and it can ensure that the collected data are more symbolic and improve the richness and credibility of the test basis. We will use the SPIRIT checklist to improve the quality of the study.

## Data Availability

Not applicable.

## Abbreviations

ACS: Acute coronary syndrome
MACE: Major adverse cardiovascular events
CHD: Coronary heart disease
STEMI: ST-segment elevation myocardial infarction
non-STEMI: Non ST-segment elevation myocardial infarction
UA: Unstable angina
MPS: Mononuclear phagocyte system
NKT cells: Nature killer T cells
ESC: European society of cardiology
ECG: Electrocardiogram
hs-cTnT: High-sensitivity cardiac troponin T
AST: Aspartate aminotransferase
ALT: Alanine aminotransferase
ACEI: Angiotensin-converting enzyme inhibitor
ARB: Angiotensin II receptor
LDL-C: Low-density lipoprotein cholesterol
RR: Relative risk
ROC: Receiver operating characteristic
EMR: Electronic medical record
